### **Abstract**

Preterm newborns are vulnerable to perinatal conditions due to their organic immaturity and associated external factors. This association can lead to neurological impairments, affecting motor development, respiratory mechanics, and the establishment of breastfeeding. Considering the current approach to the humanization of neonatal care, as well as the recent Brazilian epidemiological need for studies focused on early intervention in hospitalized newborns at risk or with established neurological problems, the necessity for therapeutic investigations that help prevent and minimize morbidities in this population becomes evident. The primary objective of this study is to evaluate the short- and medium-term effects of a physiotherapeutic intervention protocol associated with kangaroo positioning on the neuromotor behavior and clinical outcomes of preterm newborns in a neonatal unit. A randomized controlled trial with a parallel group design and balanced distribution ratio will be conducted. A total of 34 preterm newborns, with more than 72 hours of postnatal life and stable clinical conditions, admitted to Neonatal Intermediate Care Units will participate in this study. They will be randomly divided into two groups: a) Experimental Group (EG), which will receive the physiotherapeutic intervention protocol associated with kangaroo positioning; and b) Control Group (CG), which will receive only the kangaroo position. The protocol will be implemented over 10 consecutive days, with each session of the physiotherapeutic intervention lasting 15 minutes and 60 minutes of kangaroo positioning, during the period from 34 to 36 weeks and 6 days of postmenstrual age. Primary outcomes will include weight gain at the end of the protocol; Prechtl's general movements assessment at 36 weeks postmenstrual and 12 weeks post-term. Secondary outcomes will include posture and muscle tone, behavioral state, time to establish and maintain breastfeeding, duration of hospitalization, and vital signs. This study will provide experimental support for evidence-based practice, and its results may be used to guide feasible intervention protocols for the routines of neonatal unit teams in Brazilian hospitals.

**Keywords:** Early stimulation. Kangaroo method. Preterm newborn. Child development.

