### **4.2 Participants**

This study will involve 34 preterm newborns, born with a gestational age of 34 weeks or less, between 34 and 36 weeks and 6 days postmenstrual age, hospitalized in the Neonatal Intermediate Care Unit (UCIN). To estimate the minimum number of participants, considering a difference of at least 50% between the groups regarding the quality of general movements (GMs) after the intervention using the chi-square test, the suggested sample size is 13 participants per group (80% power;  $\alpha = 5\%$ ). Considering potential losses during the follow-up, two groups of 17 participants will be included. The newborns will be randomly allocated into two groups: the experimental group ( $n=17$ ), which will receive the physiotherapy intervention protocol associated with the kangaroo position, and the control group ( $n=17$ ), which will receive only the kangaroo position.

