#### *4.8.4.2. Assessments after discharge*

After hospital discharge, the GMs of babies from both groups will be assessed at 12 weeks post-term. GMA will be applied. The assessments will take place between feedings (after 1 to 1.5 hours) and should not coincide with vaccination days. The babies must be in an active alert state, i.e., state 4 (eyes open, no crying, but exhibiting gross movements) (BRAZELTON et al., 1976). The assessments will be conducted on a mat, with the baby preferably wearing only a diaper. If the baby is not cooperative, showing crying or restlessness, the assessment will be interrupted, the baby will be calmed, and the assessment will resume. If the baby remains restless, a new date will be scheduled.

The assessments will be filmed and scored later. The camera will be mounted on a tripod with sufficient distance and angle to capture the baby's full-body movements. Post-discharge assessments may take place through home visits or at the Neuropediatrics Study Laboratory (LABEN) at the Integrated School Clinic-UFMS, as per the parents'/guardians' preference. Training and agreement indices will be conducted between at least two experienced researchers/observers for assessment using the instruments, aiming for a minimum agreement index of 80%.

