### **4.9 Outcomes**

#### **4.9.1 Primary outcomes**

- **Weight Gain:** daily body weight recording as a parameter for weight tracking of preterm newborns during the application of the protocol (experimental and control).
- **Neuromotor Behavior:** assessed by the classifications of GMs achieved using the GMA (EINSPIELER et al., 1997).

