#### 4.10 Data Analysis

For the statistical analysis of the data, the statistical package SPSS 23.0 will be used. To analyze the dependent variables, the Levene's Test for Homogeneity of Variance and the Shapiro–Wilk Test for Normality will be applied. Once the assumptions are met, parametric and non-parametric tests may be applied depending on the homogeneity and normality conditions of the sample. Descriptive statistics will first be performed to characterize the sample. Treatment effects will be obtained by comparing the groups

To test differences between groups (treatment effects) for categorical variables (quality of GMs, behavioral state, success, and maintenance of breastfeeding), the chi-square test will be applied. To test differences between groups concerning body weight, the independent t-test will be used. For other continuous variables, t-tests or the Mann–Whitney test will be used to calculate differences between the groups. Adjusted means and 95% confidence intervals may also be calculated using the mixed linear model (GLM) for continuous variables, considering the interaction terms of group x days of evaluation.

To calculate the effect size of the intervention, a 95% confidence interval will be adopted, and either Cohen's d or r ( $r = \text{z-score} / \sqrt{\text{total sample}}$ ) will be considered, depending

on whether parametric or non-parametric tests are used. A significance level of  $\alpha=5\%$  will be considered for all analyses.

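### Weight gain and general movements at two time points are unranked primary outcomes, each tested at 5% with no success rule, and weight has no sample-size justification

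*Protocol*

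**What the plan says.** The Abstract gives as primary the weight gain at the end of the protocol ("Primary outcomes will include weight gain at the end of the protocol") together with "Prechtl's general movements assessment at 36 weeks postmenstrual and 12 weeks post-term".

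Section 4.9.1 lists two primary outcomes on an equal footing. Weight gain is described as "daily body weight recording as a parameter for weight tracking of preterm newborns during the application of the protocol". Neuromotor behaviour is "assessed by the classifications of GMs achieved using the GMA", with no time point attached. Section 4.8.4.1 places one GM assessment the day after the protocol ends, and section 4.8.4.2 adds that "the GMs of babies from both groups will be assessed at 12 weeks post-term".

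Section 4.10 assigns the tests. GM quality is compared by chi-square, and for weight: "To test differences between groups concerning body weight, the independent t-test will be used". It then says that a significance level of 5% "will be considered for all analyses". It gives no testing order, no division of alpha, and no statement that one, or all, of the primary outcomes must be significant.

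Section 4.2 derives 13 infants per group "considering a difference of at least 50% between the groups regarding the quality of general movements" after the intervention, at 80% power and 5% alpha, and raises this to 17 for losses. It does not mention weight.

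**The concern.** When several outcomes are all called primary and each is tested at 5%, the trial has several chances to produce a primary success. Unless the plan says that all must succeed, or in what order they are tested, the 5% describes each test and not the primary claim. Sections 2 and 4 (Relevance) say that the results may support adopting the protocol in both hospitals and serve as a model elsewhere, so it matters what counts as a positive result.

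The second issue is what the trial is sized for. The 80% power belongs to one GM comparison. Weight gain has equal primary status, but no target difference or standard deviation is given for it. Nor is any expected rate of normal GMs given for 12 weeks, where section 4.7.1 applies a different classification (fidgety movements instead of writhing movements).

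**Working it through.** **Inputs.** Primary comparisons: weight gain, GMs after the protocol, GMs at 12 weeks (Abstract). I treat the 36-week assessment and the one on the day after the protocol as the same. Section 4.9.1 can be read as two outcomes, so both counts are shown. Alpha is 5% per test (4.10), taken as two-sided because the protocol does not say. Infants per group: 13 evaluable, 17 enrolled (4.2).

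**1. The plan's own figure.** The group rates are not stated, so 50% is read as 50 percentage points and a range is run. The pooled-variance formula, with p̄ the mean of p1 and p2, is

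n = [1.96·√(2p̄(1−p̄)) + 0.842·√(p1(1−p1) + p2(1−p2))]² / (p1−p2)².

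| Rates | n per group, rounded up |
|---|---|
| 25% v 75% | 15 |
| 10% v 60% | 14 |
| 5% v 55% | 12 |
| 0% v 50% | 11 |

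The stated 13 lies inside this range. Exact enumeration of the uncorrected chi-square test with 13 per group gives 82% power for 25% v 75% and 84% for 10% v 60%. The calculation is sound for a GM comparison with a 50-point difference.

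**2. Family-wise error if any one success counts.** For k independent tests this is 1 − 0.95^k.

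- k = 2: 1 − 0.9025 = 9.75%.
- k = 3: 1 − 0.857375 = 14.26%.
- Bound for three tests of exact 5% size under any dependence: 3 × 5% = 15%.
- Three equally correlated normal statistics (simulation): 13.6% at correlation 0.3, 12.5% at 0.5, 9.9% at 0.8.

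**3. Small-sample size of the chi-square test.** The true size of a nominal 5% test depends on the underlying rate. These are exact sizes at assumed rates of normal GMs, the same in both groups:

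| Per group | 30% normal | 50% normal | 80% normal | 95% normal |
|---|---|---|---|---|
| 13 | 5.65% | 7.56% | 4.29% | 0.32% |
| 17 | 4.59% | 5.77% | 4.62% | 0.74% |

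Combine these with a 5% weight test under independence. At 30% normal after the protocol and 80% at 12 weeks, 13 per group gives 1 − 0.95 × 0.9435 × 0.9571 = 14.2%, and 17 per group gives 13.5%. At 50% and 80%, 13 per group gives 1 − 0.95 × 0.9244 × 0.9571 = 16.0%. At 30% and 95%, 17 per group gives 1 − 0.95 × 0.9541 × 0.9926 = 10.0%. The nominal figures of step 2 therefore move by a few points either way.

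**4. Weight.** Two-sample t-test, two-sided 5%, 80% power, noncentral t: the detectable standardised difference is 0.99 SD with 17 per arm and 1.15 SD with 13. The normal approximation (1.96 + 0.842)·√(2/n) gives 0.96 and 1.10. At an assumed true difference of 0.5 SD, power is 29% with 17 and 23% with 13.

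**5. GMs at 12 weeks.** No rates are given, so the following only illustrate. Exact chi-square power for 70% v 90% normal is 23% (13 per arm) to 30% (17 per arm); for 80% v 95% it is 14% to 23%. A 50-point difference would have about the power found in step 1. The protocol does not say which case applies.

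**The case against.** Several stronger readings are tempting, and the protocol does not support them.

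- **That 14% is a ceiling, or the trial's actual error rate.** It is the value for three independent tests. The bound at exact 5% size is 15%. The two GM tests use the same infants and the same method, so positive correlation, which lowers the figure, is plausible. It also requires that any one success counts, which the protocol neither states nor excludes. If all three had to succeed there would be no inflation, though power would fall.
- **That section 4.10 rules out a valid scheme.** It does not: a fixed-sequence procedure also tests each hypothesis at 5%. What is missing is the order and the success rule, and detail of that kind is often left to a SAP. But the protocol itself makes the outcomes primary without ranking them and fixes 5% throughout, so this softens the point without removing it.
- **That weight and 12-week GMs miss their stated 80% power.** No power is stated for weight, and section 4.2 names no GM time point. Twelve weeks post-term is also after the intervention, and the allowance for losses during follow-up could suggest that the later assessment was in view. Power for 12-week GMs is therefore unknown, not shown to be low.
- **That the fidgety scale makes a 50-point gain uniquely impossible.** A gain of 50 points needs a control rate of at most 50% for any proportion, including the post-protocol one.
- **That a null result would be misread.** Section 4.10 plans effect sizes and 95% confidence intervals, which would show the imprecision.

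What remains is the unranked primary outcomes at 5% each, the missing success rule, the missing size justification for weight, and the unnamed GM time point.

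**Conclusion.** The concern holds in this limited form. On the any-one-success reading, which the protocol leaves open, the nominal family-wise error for the primary claim is about 10% for two outcomes and about 14% for three independent tests. Strong positive correlation among three (0.8) brings it to about 10%. The true size of chi-square in arms of 13 to 17 shifts these values, to between about 10% and 16% in the scenarios run. Every case examined is about double the stated 5% or more.

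The sample size is reproducible for GM quality after the intervention and for nothing else. Weight gain would need a difference of about one standard deviation (0.99 SD with 17 per arm, 1.15 SD with 13) for 80% power, and the protocol does not say whether that is expected. The figures assume two-sided tests, and that the 50% in section 4.2 means percentage points.

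**What to change.** - **Sections 4.9 and 4.10.** Make GM quality at the post-protocol assessment the first or only primary test, at two-sided 5%. It is the outcome on which the sample size most plausibly rests. Test weight gain and 12-week GMs afterwards in an order fixed in advance, each at 5% only if the previous test is significant. Which of the two comes first is the sponsor's choice; the general objective covers both short- and medium-term effects. Treat the remaining outcomes as secondary, without confirmatory claims. Bring the Abstract into line.
- **Section 4.2.** State which GM time point the 80% power refers to and that it does not extend to weight, and give the detectable weight difference (about 0.99 SD with 17 per arm, 1.15 SD with 13).

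The cost is wording: no added infants or assessments, and no loss of power on the first test. The sequence holds the family-wise error at a nominal 5%. For comparison, splitting alpha equally (0.05/3 = 1.67% each) would need about 20 infants per group for 25% v 75%, or 18 for 10% v 60%, more than the 17 enrolled. The downside is that outcomes later in the sequence cannot be claimed as confirmatory if an earlier test fails.

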## 1 Introduction

Preterm birth occurs when delivery happens before completing 37 weeks of gestation or less than 259 days, counted from the first day of the last menstrual period (WORLD HEALTH ORGANIZATION, 2010), resulting in the birth of babies with biological immaturity for extrauterine life.

The frequency of preterm birth has been increasing worldwide, including in Brazil. The estimated global prevalence of preterm birth in the country for the period 2011-2012 was 11.5% (LEAL et al., 2016). According to the World Health Organization (BLENCOWE, 2013), Brazil is among the ten countries that most contribute to the rising number of preterm newborns globally. The Central-West region ranks fifth among Brazilian regions, with an incidence of 6.2% of preterm births in the country (LEAL et al., 2016). The state of Mato Grosso do Sul recorded a proportion of 11.8% of preterm births in 2015 (SINASC, 2017). These data draw the attention of public policies since perinatal conditions responsible for infant mortality in Brazil are particularly common in this newborn population (BRASIL, 2011a).

Gestational age and birth weight are some of the biological variables involved in newborn delivery. Preterm newborns with low birth weight ( $< 2500$  g) are especially vulnerable to perinatal conditions due to several organic and external factors. Organic immaturity, particularly of the pulmonary and neurological systems, compromises gas exchange, increasing the risk of death and morbidities related to neurological impairments (BRASIL, 2011a). The inefficient production of surfactant (LEMOS; MAUX; PAIVA, 2013), associated with structural immaturity, imposes significant limitations on early extrauterine breathing (FRIEDRICH; CORSO; JONES, 2005). These newborns may experience variability in gas exchange, leading to periods of hypoxia and hyperoxia, hypo- or hypercapnia, altering the brain blood flow autoregulatory capacity and increasing the risk of brain injuries (LIEM; GREISEN, 2010). This condition can compromise brain oxygenation and, consequently, the organization and functioning of the central nervous system during a period of significant development (ALBERTINE, 2012; HAGBERG; JACOBSSON, 2005).

Neuromotor system immaturity is another intrinsic barrier to the normal development of preterm newborns. Due to this immaturity and environmental factors, preterm newborns may not experience adequate movement. Without appropriate experiences, they are less capable of perceiving stimuli, and with altered perception, they are less able to learn (DE GROOT, 2000) and perform spontaneous movements against gravity (GRENIER et al., 2003; VAIVRE-DOURET et al., 2004). The human fetus exhibits specific movement patterns generated

endogenously, emerging between the 9th and 12th postmenstrual weeks and continuing after birth, regardless of when birth occurs. These early spontaneous motor patterns include the so-called general movements, which are present from early fetal life until the 5th month after term age (EINSPIELER; PRECHTL, 2005; EINSPIELER et al., 1997).

During the preterm period, normal general movements involve the whole body, occur frequently, and last long enough to be observed. They follow a variable sequence of arm, leg, neck, and trunk movements, increasing and decreasing in intensity, strength, and speed, with gradual onset and end. Rotations along the limb axes and small directional changes make these movements fluid and elegant, giving the impression of complexity and variability (EINSPIELER; PRECHTL, 2005). From term age until the 6th or 9th post-term week, general movements take on an elliptical form and are characterized by moderate-speed movements with smaller amplitude, closer to the midline, known as writhing movements. From the preterm period to the 9th post-term week, motor patterns differing from the described general movements are considered abnormal and can be classified as poor repertoire, characterized by monotonous movement sequences; cramped-synchronized, involving rigid movements lacking the normal smooth and fluent character; or chaotic, characterized by large-amplitude movements devoid of fluency and elegance (EINSPIELER; PRECHTL, 2005; EINSPIELER et al., 1997).

Around the 6th to 9th post-term week, a shift occurs in movement patterns of the limbs, trunk, and head, as writhing movements gradually disappear while new movements with lower amplitude, moderate speed, and variable acceleration emerge in all directions. These movements, present continuously while the baby is awake, are called fidgety movements. These movements are typically continuous and most evident from the 9th to the 15th-20th post-term week, gradually disappearing as intentional movements begin to emerge. Abnormal or absent fidgety movements indicate a higher risk of later neurological dysfunctions, whereas normal fidgety movements are predictive of normal development (EINSPIELER; PEHARZ; MARSCHIK, 2016; EINSPIELER; PRECHTL, 2005; EINSPIELER et al., 1997).

Preterm newborns, due to biological and environmental factors, may experience limited spontaneous movement during their stay in neonatal care units (BRACEWELL, MARLOW, 2002) when compared to full-term newborns (FALLANG et al., 2005). These newborns may exhibit monotonous, rigid, or irregular movement sequences due to impaired postural control (FALLANG et al, 2005), losing the characteristics of fluency, complexity, and variability of spontaneous movements, as well as displaying less evident fidgety movements (EINSPIELER; PEHARZ; MARSCHIK, 2016).

Associated with organic factors, external or environmental factors necessary for the clinical care of preterm newborns in intensive care units can cause deficits in motor, sensory, mental, and emotional aspects. External factors such as maternal separation and inadequate sensory stimulation, sometimes with insufficient stimuli or excessive ones, enhance the risks for morbidities and negatively impact proper development.

All references to the initial relationships between the mother and preterm newborn are altered in the face of the separation of the dyad in the neonatal unit. This separation limits the formation of the mother-child bond, hinders the breastfeeding process (AMIN et al., 2000; BRASIL, 2009; SANTORO JUNIOR; MARTINEZ, 2007), and interferes with the organization and development of brain circuits involved in language and social communication (CALDAS, 2016). Thus, the preterm newborn is initially susceptible to the deprivation of the benefits of breastfeeding and to socio-communicative problems in their development. As an aggravating factor, preterm newborns, during the early stages of central nervous system development, are routinely subjected to painful procedures and excessive sensory stimulation in neonatal units (CARBAJAL et al., 2005; SHAREK et al., 2006; SIMONS et al., 2003). Such stimuli can lead to changes in pain processing, behavioral changes, and reduced volume in sensory brain areas (GASPARDO; LINHARES; MARTINEZ, 2005; LAGO et al., 2009; NEWNHAM; INDER; MILGROM, 2009).

Along the developmental trajectory, in addition to risk factors, which expose newborns to multiple and continuous adverse events, there are also protective factors for development. When the response to these events is frequent, intense, or prolonged and is associated with the absence or scarcity of protective factors, the negative impact, particularly on the neurological system, can be extremely toxic. There is a link between exposure to early adversities, leading to toxic stress, and subsequent deficiencies in learning, behavior, and physical and mental well-being (SHONKOFF; GARMER, 2012). Moreover, prolonged hospitalization negatively influences the motor (PANCERI et al., 2012) and socio-communicative (CALDAS, 2017) development of babies hospitalized for more than thirty days, placing the preterm newborn population under considerable vulnerability to problems in social, cognitive, and motor development. The consequences of this exposure may be transient, but they can also result in chronic motor development dysfunctions that extend beyond the neonatal period (FORMIGA; LINHARES, 2009).

In recent decades, the effects of prematurity on motor development have been reported in several studies, which pointed to significant differences in the motor development of preterm and term newborns, with lower scores in motor evaluation outcomes for preterm babies

(FORMIGA et al., 2015; FUENTARIA; SILVEIRA; PROCIANOY, 2017). For example, preterm babies showed a tendency to exhibit disadvantages in manual skills behavior between 3 and 8 months of corrected age (HEATHCOCK; LOBO; GALLOWAY, 2008; SOARES-MARANGONI; VON HOFSTEN; TUDELLA, 2012), less skill in more refined manual tasks (SOARES-MARANGONI; CUNHA; TUDELLA, 2014), lower ability to sit (FORMIGA; CEZAR; LINHARES, 2010), and greater motor delay in sitting and standing postures at 8 months of corrected age (PIN et al., 2009). In school age, children born preterm are more susceptible to developmental impairments in motor, behavioral, and academic performance areas (MOREIRA; MAGALHÃES; ALVES, 2014), typically showing worse motor coordination and a higher incidence of cerebral palsy than those born at term (ODD et al., 2013). These children may exhibit reduced corticomotor excitability in brain areas associated with motor control, even without cerebral injury (PITCHER et al., 2012).

Preterm newborns also have greater vulnerability to socio-communicative problems (CALDAS et al., 2016; GUINCHAT et al., 2012) when compared to term newborns (DE SHUYMER et al., 2011; SHAH et al., 2013). Some studies report that preterm newborns may exhibit atypical behavioral characteristics, such as difficulty in maintaining visual attention before three months, longer processing time in response to stimuli (SHAH et al., 2013), less active exploration of objects, and reduced joint activities with the mother (DAWSON et al., 2012).

These studies demonstrate that the factors associated with prematurity can result in motor development problems in the medium and long term, thus reaffirming the need for evaluation, monitoring, stimulation, and early intervention measures with an emphasis on preventing these problems in preterm newborns (FORMIGA; PEDRAZZANI; TUDELLA, 2004).

To minimize the negative effects of prematurity on child development, changes were made in hospital practices to better adapt the baby to extrauterine life. Since the 1990s, the Ministry of Health has incorporated the Kangaroo Method into health policies as a strategy for humanizing neonatal care and promoting family citizenship, thereby maximizing protective factors for the development of preterm newborns (BRASIL, 2013; 2014). The Kangaroo Method includes humanized care, skin-to-skin contact between the newborn and their parents, environmental control, pain reduction, family care, and support from the health care team (BRASIL, 2016). Despite these efforts, hospital units still expose newborns to discomfort and pain within their routine care (REICHERT; LINS; COLLET, 2007), leading to stress, increased energy expenditure, risk of hypoxia, and breastfeeding difficulties (GRUNAU, 2002).

Therefore, interdisciplinary therapeutic measures are necessary to improve the comfort of preterm newborns (GASPARDO; LINHARES; MARTINEZ, 2005) to favor the success of breastfeeding and the motor and socio-communicative development of this population. One therapeutic measure used within the Kangaroo Method to promote the care of newborns in neonatal units is the Kangaroo Position, which provides a containment experience simulating the intrauterine environment from which the newborn has been deprived. The Kangaroo Position involves keeping the newborn in a vertical position, skin-to-skin, against the parent's chest, with the baby wearing only a diaper. Kangaroo positioning begins early and increases progressively, at the family's free choice, for as long as both parties find it enjoyable and sufficient. However, each time the baby is placed in this position, it is recommended that the baby stays for at least one hour to receive its benefits. It should be performed in a guided, safe manner and with the support of a trained healthcare team (BRASIL, 2013; 2016). The Kangaroo Position positively influences the newborn's cardiorespiratory function. The slightly inclined vertical position during Kangaroo positioning favors respiratory mechanics, increasing diaphragm efficiency and lung function, with improvements in respiratory patterns and a reduction in grunting (LUDINGTON-HOE et al., 1999), peripheral oxygen saturation (BERA et al., 2014; HUNT, 2008; LUDINGTON-HOE; FERREIRA; GOLDSTEIN, 1998; SOUKKA et al., 2014), reduction in respiratory rate (BERA et al., 2014; FOHE; KROPF; AVENARIUS, 2000), and maintenance of heart rate within normal ranges (BEGUM et al., 2008; BERA et al., 2014).

Most studies have pointed out the benefits of the Kangaroo Position on the motor development and behavior of preterm newborns in the short, medium (BARRADAS et al., 2006; DAVID et al., 2012; DINIZ et al., 2013; MOTA; SÁ; FROTA, 2005; PADILHA; STEIDL; BRAZ, 2014), and long term (FELDMAN; ROSENTHAL; EIDELMAN, 2014; SCHNEIDER et al., 2012), generalized movements of the newborn (REINAUX, 2005), establishment of exclusive breastfeeding (JAYARAMAN et al., 2017; SANTOS; AZEVEDO FILHO, 2016; PADILHA; STEIDL; BRAZ, 2014), improvement in mother-infant interaction (NUNES et al., 2017), better weight gain and growth (EVEREKLIAN; POSMONTIER, 2017; SHARMA; MURKI; PRATAP, 2016), and reduction in stress and pain (MAIA; AZEVEDO; GONTIJO, 2011; RUSH, 2016; SANTOS; AZEVEDO FILHO, 2016). Preterm newborns subjected to Kangaroo Position show an increase in physiological flexor tone (DINIZ et al., 2013), assuming a posture of greater limb flexion, associated with greater trunk flexion when assessed using the Dubowitz method (BARRADAS et al., 2006; GHISI; IWABE; TORELLO, 2004; MOTA; SÁ; FROTA, 2005). Some authors also suggest that Kangaroo positioning may

have a positive effect on motor development in preterm newborns when assessed using the Alberta Infant Motor Scale (DAVID et al., 2012).

On the other hand, other studies investigating the effects of the Kangaroo Position on generalized movements of preterm newborns found no significant differences in these movements before and after positioning (CONSTANTINO et al., 1999). Another study, using the Test of Infant Motor Performance (TIMP), observed that babies subjected to the same positioning initially presented motor performance above expectations but showed delays in hip and lower limb movements during antigravity movements and standing position at 44-48 weeks of corrected age (REINAUX, 2005), suggesting that another intervention could be considered in conjunction with the Kangaroo Position. Shaikh and Namrata (2017) compared two groups of preterm newborns: one group received therapeutic massage associated with Kangaroo Position, and the other received only the Kangaroo Position. The authors concluded that the group combining therapeutic massage with the Kangaroo Position showed more significant improvement in physiological and behavioral states compared to the group that received only the Kangaroo Position.

Due to its numerous benefits and being a safe, low-cost intervention, the Kangaroo Mother Method can be implemented in any hospital and provides the multiprofessional team with an important additional resource in the care and attention of preterm infants and their families (BOUNDY et al., 2016; PADILHA; STEIDL; BRAZ, 2014). When designing interventions for Kangaroo Mother care, contextual factors and sociocultural norms need to be taken into consideration (CHAN et al., 2016). The physiotherapist in the neonatal unit, as part of the multiprofessional team, should focus on the physiological, respiratory, and motor needs of the preterm newborn, establishing an appropriate relationship and interaction between the baby and the family, as well as stimulating and clarifying the importance of the Kangaroo Position (AZEVEDO; CALIXTO; ABREU, 2017; BRADY; SMITH, 2015; SWEENEY et al., 2010).

Another important strategy to improve the development of preterm newborns are early intervention programs, initiated still in the hospital environment, with the aim of enhancing the child's social, cognitive, and motor development. Early intervention can be seen as a set of neurodevelopmental evaluation actions and therapies practiced through motor and sensory stimulation with the goal of ensuring adequate development for preterm newborns, promoting an efficient transition from the hospital environment to the community and home (GARCIA; GEPHART, 2013; OBERG et al., 2012). The preterm newborn is unable to maintain postural organization due to their muscle hypotonia and difficulty in self-organization. This, combined

with the positioning in the wide environment of the incubator/cradle and the action of gravity, facilitates the fixation of the newborn in an extended posture, favoring the development of muscle retractions, which may lead to delays in motor development (CARVALHO; SIQUEIRA, 2013) and spontaneous movement (CABRAL; SCHETTINO; POMPEU, 2015; EINSPIELER; PEHARZ; MARSCHIK, 2016). Early intervention handling aims to facilitate the maturational adjustment of the flexor chain (FERREIRA; SANTOS, 2016), in order to stimulate the body organization to favor spontaneous global movement (RAMACHANDRAN; DUTTA, 2013). Intervention in the first few months of life helps in the modulation of muscle tone, improving posture, enhancing motor skills (MARLOW, 2004), and consequently providing appropriate motor experiences.

Early intervention programs for preterm newborns have a positive influence on cognitive and motor outcomes during childhood, with persistent cognitive benefits during preschool age (SPITTLE, 2015; VANDERVEEN et al., 2009). A systematic review with meta-analysis compiled evidence on motor intervention for preterm newborns and suggested that interventions that extend beyond the neonatal care period may have an impact on the motor development of preterm infants, with the strongest effects observed before 6 months of age, particularly when interventions were specifically directed at motor skills (HUGHES; REDSELL; GLAZEBROOK, 2016). Another review linked the components of early intervention (education and psychosocial support for parents and support for child development) to maternal psychosocial aspects and observed that interventions including psychosocial support resulted in better outcomes for mothers of preterm infants (BENZIES, 2013). The integration of the family is necessary for the success of early intervention programs (FORMIGA; PEDRAZZANI; TUDELLA, 2010; OBERG et al., 2012; SWEENEY, 2010). In general, early intervention aims to promote the baby's interaction with the environment through sensorimotor stimuli, leading to responses closer to the normal pattern and inhibiting the learning of inappropriate postures and movements (GONÇALVES, 2012). These stimuli must be carefully designed based on a thorough evaluation of the preterm newborn and follow their neuroplastic phases, meaning the amount of stimuli should be closely related to the capacity, interest, and possibilities of each newborn (FORMIGA; PEDRAZZANI; TUDELLA, 2010).

Among the standardized instruments for identifying atypical motor patterns, we highlight Prechtl's method for assessing General Movements (GMA). It allows a qualitative assessment of movements, is non-invasive and non-intrusive, and is used as a diagnostic tool for early detection of brain dysfunction, considered an advance in predicting

neurodevelopmental impairment (EINSPIELER; PRECHTL, 2005; EINSPIELER; PEHARZ; MARSCHIK, 2016; NOVAK et al., 2013). For newborns discharged from neonatal intensive care units, it is important to use reliable scales and methods with proven sensitivity and specificity to properly direct this population to early intervention programs.

Based on the context outlined and considering that there is insufficient evidence using a physiotherapeutic intervention protocol associated with Kangaroo Position in neonatal units, some questions arise: a) Is the combination of a physiotherapeutic protocol with Kangaroo Position more effective in improving clinical outcomes, including body weight, breastfeeding, behavioral state, length of hospital stay? b) Is the combination of a physiotherapeutic protocol with Kangaroo Position more effective in improving posture and tone, and normalizing general movements, in newborns with poor motor repertoire than Kangaroo Position alone?

Considering the evidence that early intervention (SYMINGTON; PINELLI, 2016) and Kangaroo Position (NUNES et al., 2017) improve self-regulation and the mother-infant bond, it is hypothesized that the application of the physiotherapeutic intervention protocol associated with Kangaroo Position over fifteen days in stable preterm newborns hospitalized in a neonatal unit will lead to an improvement in clinical outcomes while safely maintaining vital signs. As a consequence, and based on the beneficial effects of Kangaroo Position (SANTOS; FILHO, 2016) and early intervention (MARLOW, 2004) on body posture, muscle tone, and spontaneous movement, it is expected that these newborns will show better motor patterns immediately after the protocol, and at 12 weeks post-term, compared to control newborns.

